### Quality control

#### Face validity

Face validity concerns whether or not a test assesses what it is designed to measure. It will examine whether the questionnaire asks all the relevant questions and uses the appropriate language and language level [34]. The questionnaire will be given to three groups: supervisors, Family Medicine Specialists (FMS), and pilot MSM. Face validity will be conducted among a few MSM living with HIV in Bandar Botanik Health Clinic in Klang, Selangor. The feedback from the supervisors and the MSM upon the face validity will be assessed and amended.

#### Content validity of the questionnaire

A forward and backward questionnaire translation was done according to the WHO translation guidelines. The English language expert personnel did the forward translation while the researcher did the backward translation. Then, the backward translation questionnaire was compared with the original questionnaire. After that, the questionnaire underwent content validity. The purpose of content validity was to look for the magnitude in which the questionnaire’s items thoroughly represented the construct of interest. For this study, the questionnaire was reviewed and discussed with two Public Health specialists, the Head of the HIV Unit and the Non-Communicable Disease (NCD) Unit from Selangor State Health Department and HIV Non-Governmental Organizations (NGO) representatives.

### Qualitative data collection method and process

#### Interview guide for in-depth interviews

The development of the interview guide for the in-depth interview is based on the biopsychosocial approach to help explain why the independent variables tested in the first phase were significant predictors of depressive symptoms. The interview protocol will next be tested on a subset of MSM from the pilot quantitative study with moderate to severe depression. This procedure will improve the quality of the questions through the MSM’s input and the interviewer’s familiarity with the questions.

#### Field visit

A field visit is one of the crucial steps in qualitative data collection. Before collecting the data, the researcher will develop a rapport with the health clinic staff and seek familiarity with the location. This step also allows the researcher to meet the health clinic’s authority: the Family Medicine Specialist (FMS), the medical officer, the matron, sister in charge of the HIV clinic to obtain permission. A room or place will be designated to maintain privacy while collecting data. At that time, a brief presentation on the study procedure will be conducted to explain the data collection work process.

#### Study sampling and procedure for qualitative phase

Purposive sampling will be chosen in the qualitative phase. The MSM will be chosen from those with moderate to severe depressive symptoms or those with a PHQ-9 score of ≥ 10 from the quantitative study. Sample size guidelines suggested an adequate range between 20 and 30 interviews [35]. Therefore, 20 MSM will be selected for the qualitative study. Suppose all or most MSM in the quantitative phase have moderate to severe depressive symptoms. Those with severe depressive symptoms will be chosen first, followed by moderately severe depressive symptoms and moderate depressive symptoms. The justification for this method is that the quantitative and qualitative data and their analysis might clarify and explain the statistical results through a more in-depth examination of the MSM’s perspectives.

The study sampling is relatively small compared to the quantitative method, as it depends on the saturation point where no new information is acquired from the following interview. Data saturation is achieved when: (1) there is adequate information to replicate the study; (2) when the capacity to acquire new information has been attained; and (3) when further coding is no longer feasible [36].

Only the main researcher will conduct the in-depth interview for the qualitative study. The researcher will approach the selected MSM at the clinic during clinic visits. The researcher will explain the study protocol and obtain written consent from the participants after a clinic appointment in the consultation room or any available room in the clinic. The room used for the interview will be identified prior to the interview with permission from the clinic’s head. Subsequently, an in-depth interview will be conducted to obtain the information required and will be voice recorded using two voice recorder devices. The interview will require MSM to tell their experiences regarding their depressive symptoms according to the biopsychosocial approach.

### Statistical methods and analysis

#### Sample size calculation

The sample was chosen based on a study by Perdue et al. (2003) [37], as this study gave the highest number of samples and the most feasible numbers to execute this research within the time frame.

P1 = 0.55 (Proportion of depression among MSM with education below college)

P2 = 0.45 (Proportion of depression among MSM with education level at college or higher)

$$\text{n}=\;\frac{\left\{1.96\;\surd 2\left(0.55\right)\;\left(1-0.55\right)\;+\;0.62\surd \;\left(0.55\left(1-0.55\right)\right)\;+0.45\left(1-0.45\right)\right\}2}{\left(0.55-0.45\right)2}$$

n = 392

Considering adjustment for comparison between 2 groups

= 392 x 2

= 784

Considering adjustment for non-response of 20%

= 784 + [(0.2) (784)] = 941

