**Methods:**

The study has ethical approval from the Medical Research Ethics Committee (MREC) of the Ministry of Health (MOH) NMRR ID-21-02210-MIT. This study will apply an explanatory sequential mixed methods study design. It comprised two distinct phases: quantitative and qualitative study design for answering the research questions and hypothesis. This study will randomly recruit 941 MSM living with HIV in the quantitative phase, and at least 20 MSM living with HIV purposively will be selected in the qualitative phase. The study will be conducted in ten public Primary Care Clinics in Selangor, Malaysia. A self-administered questionnaire will gather the MSM’s background and social, psychological, and biological factors that could be associated with depressive symptoms. For the quantitative study, descriptive analysis and simple logistic regression will be used for data analysis. Then, variables with a P value < 0.25 will be included in multiple logistic regression to measure the predictors of depressive symptoms. In the qualitative data collection, in-depth interviews will be conducted among those with moderate to severe depressive symptoms from the quantitative phase. The thematic analysis will be used for data analysis in the qualitative phase. Integration occurs at study design, method level, and later during interpretation and report writing.

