### Sampling methods

A proportionate random sampling was applied. The HIV databases from each clinic were obtained from the Selangor State Health Department to look for the list and the total number of patients in each clinic. Then, the required number of MSM in each clinic was calculated based on proportion to get 941 MSM. To build trust with the MSM and ease the data collection process, the researchers engaged with HIV clinic nurses and appointed them as research nurses. Next, the lists of MSM in each clinic were obtained to screen them for inclusion and exclusion criteria. Based on the screened name list of MSM in each clinic, random sampling is conducted to select the required number of MSM using a randomizer application. New master lists of selected MSM were extracted in an Excel sheet that contained their personal information, clinical information, and the clinic appointment date to remind the researcher to ask for written consent and to collect the data when the MSM visit the clinic. From the list, the researcher will create and insert a code to replace the MSM’s names on the questionnaire and during the in-depth interview.

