#### Data analysis for quantitative study

Data will be collected and analyzed using the IBM Statistical Package for Social Science (SPSS) version 25, involving descriptive and inferential statistics. The descriptive statistics will describe the MSM’s characteristics: mean, standard deviation, mode, median, interquartile range, and percentage. Cross-tabulation and frequency counts will be used to assess the demographic items and the MSM’s responses to survey scales. The data analysis utilizes both univariate and multivariate statistical methods. Simple logistic regression will be used to measure the associations between independent and dependent variables. A less rigorous threshold, such as a P-value < 0.25, should be applied to prevent omitting crucial variables from a model due to stochastic variation [38, 39]. Therefore, variables with a P value < 0.25 will be included in multiple logistic regression to measure the predictors of depressive symptoms. The binary outcomes of depressive symptoms will use a cut-off score ≥10. The scores of 0 to 9 represent none to subthreshold depression, and a score of 10 and above represents a patient’s spectrum to possible major depression [40]. The level of significance at 0.05 and 95% confidence interval (CI) will be used to yield a significant result.

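### The 20% non-response allowance multiplies 784 by 1.2 instead of dividing by 0.8, so 941 selected patients would yield about 753 respondents, 31 fewer than required (minor)

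*Protocol article*

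**What the plan says.** The Sample size calculation section compares the proportion with depression between MSM with education below college (0.55) and those at college level or higher (0.45). It arrives at 392 per group and doubles this to 784 for the two groups. It then makes an adjustment for 20% non-response, printed as "784 + [(0.2) (784)] = 941".

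The Sampling methods section applies that total to the clinic lists: "the required number of MSM in each clinic was calculated based on proportion to get 941 MSM". Names are then drawn at random from the screened lists. The list of selected men serves to prompt the request for written consent and the data collection at a later clinic visit. The Quantitative data collection section likewise puts consent and the questionnaire after the approach in clinic.

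The abstract describes the same figure differently: "This study will randomly recruit 941 MSM living with HIV in the quantitative phase".

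**The concern.** An allowance for non-response should leave the required number once the expected share has dropped out. Non-response removes a fraction of the people selected, not a fraction of the people needed. Adding 20% of 784 therefore under-corrects, because 20% of the larger figure of 941 is more than the number that was added.

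At stake is the headline size of the quantitative phase, which appears in the abstract, the sampling section and the calculation. As written, it is presented as absorbing 20% non-response, and it does not. The abstract adds to the problem by calling 941 the number recruited, although the allowance for people who will not take part is already inside it.

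**Working it through.** **Inputs.** From Sample size calculation: proportions 0.55 and 0.45, n = 392 per group, total 784, non-response 20%, final figure 941. From Data analysis for quantitative study: significance level 0.05, which matches the 1.96 in the formula. From Sampling methods: 941 is the number drawn, before consent.

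**Reproducing the plan's figure.** 392 × 2 = 784. 784 + 0.2 × 784 = 784 × 1.2 = 940.8, rounded to 941. The printed result follows from the printed operation.

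**What 941 delivers at the plan's rate.** 941 × (1 − 0.20) = 752.8, about 753 respondents. The shortfall is 784 − 753 = 31, and 31/784 = 4.0%.

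**What would deliver 784.** 784/(1 − 0.20) = 980 selected, which is 39 more than 941.

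**What 941 can absorb.** 1 − 784/941 = 0.167, so at most 16.7% non-response.

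None of these results needs a power assumption. They use only 784, 20% and 941.

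**Effect on power, under stated assumptions.** The protocol states no power. The standard two-proportion formula with pooled null variance, two-sided 0.05 and no continuity correction gives 392 per group at 80% power, so 80% is the value that 392 implies. With 0.55 against 0.45 and equal groups:

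| Respondents | Per group | Power |
|---|---|---|
| 784 | 392 | 80.1% |
| 752.8 | 376.4 | 78.5% |

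The loss is 1.6 percentage points.

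**A conflict that limits the power figures.** The formula prints 0.62 as its power multiplier, which corresponds to about 73% power. With 0.62 it gives about 332 per group (pooled proportion 0.50), or about 329 with the printed 2(0.55)(0.45) term. Neither is 392. A multiplier of 0.84 with the pooled proportion gives 390.8, and the unrounded multiplier gives 392 after rounding up. The check above takes the plan's 784 as its requirement. The multiplier is a separate matter.

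**The case against.** The strongest counter-argument is that 941 may mean participants. The abstract speaks of recruiting that number, and the Sampling methods section of getting it. With 941 actual respondents the sample would exceed 784 and there would be no shortfall. This reading does not survive the Sampling methods section, which draws the number from lists and asks for consent afterwards. Men can be approached at several kinds of appointment, which may raise response, but no replacement of non-responders is described. What stands is that the abstract's wording is open to both readings and needs settling.

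A second objection is that the effect is small, and that stands. The 20% is a planning figure given without a source, the shortfall is 4%, and no hypothesis or analysis rule changes.

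A third objection is that the power figures are fragile, and that also stands. They assume equal education groups, but education is observed in a random sample, not allocated. The documents give no split. If it were 40:60, power at 784 would be about 78.5%, as large a loss as this error causes. At 30:70 it would be 72.9%.

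A reader might go further and infer that every comparison in the study is short by 31, or that a stated power is missed. The documents support neither. The calculation sizes only the education comparison and sets no requirement for stigma, social support, CD4 or the other factors, and no power is stated anywhere. If the printed 0.62 were taken at face value, the requirement would be about 660 in total (2 × 330), and 753 would exceed it. The shortfall is therefore measured against the plan's stated 784.

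**Conclusion.** The non-response line is wrong as written, and the error is minor. At the plan's own 20% rate, 941 selected patients give about 753 respondents, 31 (4%) fewer than the 784 set for the education comparison. The figure covers non-response of up to 16.7%. This rests on 941 being the number selected, as the Sampling methods section has it, and on 784 being the requirement. The power consequence, about 78.5% against 80.1%, rests further on an inferred design power of about 80%, equal groups, 55% against 45%, and two-sided 0.05. It should be quoted only with those labels. The error does not undermine the study. It means that the stated allowance does not do what it is said to do.

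**What to change.** Correct the non-response line in Sample size calculation. Either say that 941 selected covers at most 16.7% non-response, or say that at 20% it gives about 753 respondents. Note that 784/0.80 = 980 is the figure that would cover 20%. If a power is quoted for 753, label it as an assumption with the conditions given above.

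In the abstract, distinguish the number selected from the number responding. The protocol gives February 2023 as the end of quantitative data collection, so the actual counts of men selected, approached and responding should replace the projection once available.

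Separately, reconcile the printed multiplier of 0.62 with n = 392 and state the design power.

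The cost is a few lines of text. No extra enrolment is needed, and no analysis changes.

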#### Data analysis for quantitative study

Data will be collected and analyzed using the IBM Statistical Package for Social Science (SPSS) version 25, involving descriptive and inferential statistics. The descriptive statistics will describe the MSM’s characteristics: mean, standard deviation, mode, median, interquartile range, and percentage. Cross-tabulation and frequency counts will be used to assess the demographic items and the MSM’s responses to survey scales. The data analysis utilizes both univariate and multivariate statistical methods. Simple logistic regression will be used to measure the associations between independent and dependent variables. A less rigorous threshold, such as a P-value < 0.25, should be applied to prevent omitting crucial variables from a model due to stochastic variation [38, 39]. Therefore, variables with a P value < 0.25 will be included in multiple logistic regression to measure the predictors of depressive symptoms. The binary outcomes of depressive symptoms will use a cut-off score ≥10. The scores of 0 to 9 represent none to subthreshold depression, and a score of 10 and above represents a patient’s spectrum to possible major depression [40]. The level of significance at 0.05 and 95% confidence interval (CI) will be used to yield a significant result.

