### Hypothesis

Hypothesis 1: There is a significant association between social factors and depressive symptoms among MSM living with HIV.

Hypothesis 2: There is a significant association between psychological factors and depressive symptoms among MSM living with HIV.

Hypothesis 3: There is a significant association between biological factors and depressive symptoms among MSM living with HIV.

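### Three domain-level hypotheses are tested only through single variables at 0.05, with no joint test; separately, the P < 0.25 screen makes retained results too optimistic and can lose suppressed predictors

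*Protocol article*

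**What the plan says.** The Hypothesis section sets out three statements, each about a whole domain: "There is a significant association between social factors and depressive symptoms among MSM living with HIV"; "There is a significant association between psychological factors and depressive symptoms among MSM living with HIV"; "There is a significant association between biological factors and depressive symptoms among MSM living with HIV".

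The section Data analysis for quantitative study then works one variable at a time. The outcome is binary: "The binary outcomes of depressive symptoms will use a cut-off score ≥10". First, "Simple logistic regression will be used to measure the associations between independent and dependent variables". Next, "variables with a P value < 0.25 will be included in multiple logistic regression". The reason given for the lenient threshold is "to prevent omitting crucial variables from a model due to stochastic variation". Finally, "The level of significance at 0.05 and 95% confidence interval (CI) will be used to yield a significant result".

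The section describes no joint test of a domain and no multiplicity adjustment, and it forces no variable into the multiple model. It does not say how single-variable results confirm or refute a domain hypothesis.

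**The concern.** There are two distinct problems.

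**Hypotheses and tests do not match.** A statement about a domain calls for one test of that domain. The written route gives many tests of single variables, each at 0.05. The natural way to turn those into an answer is to call a domain supported when any of its variables is significant, and that has a false-positive rate far above 5%.

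**The screen has its own effects.** Variables that survive were chosen on the same data for having small P values, so their later P values and intervals ignore the selection. A variable whose crude association is cancelled by a correlated factor can also be discarded before adjustment could reveal it. The stated reason for 0.25 is chance omission; it does not cover this systematic kind.

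Both carry into phase two. The interview guide is built to explain the significant predictors, the themes are fixed in advance from those predictors (Transferability section), and the joint display starts from the quantitative results. A chance finding can become a theme, and a masked predictor may never become one.

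**Working it through.** **1. The plan's own figure.** The article computes only a sample size. With proportions 0.55 and 0.45, two-sided 0.05 and z = 0.842 (80% power), n = {1.96·√(2·0.5·0.5) + 0.842·√(0.55·0.45 + 0.45·0.55)}² / 0.10² = 391.4, so 392 per group. Then 392 × 2 = 784 and 784 × 1.2 = 941. (The printed 0.62 does not give 392; that is a separate matter.) At 20% non-response, 941 × 0.8 ≈ 753 respondents. The article states no error rate for the hypotheses, so there is none to reproduce.

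**2. Number of candidates** (Study instruments section). Section 1 lists 13 items. Stigma has 4 subscales (or 1 total), social support 1 total (or 3 subscales), high-risk behavior 1, and substance use 3 (1 to 5 depending on how items are combined). Base count: 13 + 4 + 1 + 1 + 3 = 22. Lowest: 13 + 1 + 1 + 1 + 1 = 17. Highest: 13 + 4 + 3 + 1 + 5 = 26.

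**3. Chance of at least one significant variable under no association.** For k independent tests it is 1 − 0.95^k.
- k = 17, 22, 26: 58.2%, 67.6%, 73.6%.
- Assumed split 11/5/6: 43.1%, 22.6%, 26.5%.

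Simulating the written two-step procedure (753 respondents, 22 null independent candidates, split 11/5/6) gives about 42%, 23% and 25% per domain and 67% overall.

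With pairwise correlation 0.3 (784 respondents), the overall rate is 41%, 50% and 58% for 17, 22 and 26 candidates.

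**4. Is the screen the cause?** With 22 independent candidates the overall rate is 67% with the screen and 69% without it. At correlation 0.3 it is 50% with and 68% without. The screen does not raise the rate; the number of unadjusted tests does.

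**5. What the screen does to survivors.** A null variable passes with probability 0.25 and is significant with probability about 0.05, so among null survivors the rate is about 0.05 / 0.25 = 20%. Simulation gives 20% for independent predictors and 14–15% at correlation 0.3. Per candidate the error stays at about 5% or below.

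**6. Suppressed predictors.** If the crude effect is exactly null, the screen drops the variable in 1 − 0.25 = 75% of samples, whatever its adjusted effect. For two predictors with adjusted odds ratios 1.3 and 1/1.8 per SD and correlation r, the crude log odds ratio of the first is roughly ln 1.3 − r·ln 1.8 = 0.262 − 0.588r. Power to detect the first predictor:

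| r | Crude log OR | Without screen | With screen |
|---|---|---|---|
| −0.5 | 0.556 | 82% | 82% |
| 0 | 0.262 | 93% | 93% |
| 0.3 | 0.086 | 92% | 47–50% |
| 0.5 | −0.032 | 84–85% | 16–18% |

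With both effects in the same direction at r = 0.5, power is 81% either way. Ranges are across repeat runs.

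**7. Joint tests instead.** Three block tests in the unscreened model have about 5–7% error each. Together, at 0.05 each, they give 1 − 0.95³ = 14.3%. With Holm the family-wise rate is about 1 − (1 − 0.05/3)³ = 4.9% (simulated 4.8–5.3%).

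**8. Is a full model feasible?** At the 43–58% prevalence cited in the Introduction, 753 respondents give 753 × 0.43 ≈ 324 to 753 × 0.58 ≈ 437 cases, and at least 753 × 0.42 ≈ 316 non-cases. For an assumed 30 parameters (categorical items need several), that is 316 / 30 ≈ 10.5 or more. At an assumed 20% prevalence it is 151 / 30 ≈ 5.

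**The case against.** The strongest reply has four parts.

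- **The study identifies predictors.** The general objective suits variable-level analysis, and the hypotheses can be read as headings over it. No sentence says that one significant variable makes a domain significant. A condensed article may also leave the decision rule to a fuller plan. It stands that the any-variable rule is an inference, so the rates in step 3 are conditional on it. But the hypotheses and the per-variable route are both fixed in the text, and they do not meet.
- **The 0.25 rule is prespecified, lenient and cited.** True, and a reader might infer that it causes the high false-positive rate. Step 4 shows that it does not. Nor does the 20% figure mean that each candidate has a 20% error; it is conditional on passing the screen.
- **Masking needs opposing effects.** A reader might infer that confounded predictors are lost in general. They are not: step 6 shows no loss at zero or negative correlation, or when the effects run the same way. The example at r = 0.5 is close to exact cancellation, and the article gives no correlations. Loss of a suppressed predictor is a risk, not a certainty.
- **Prevalence may be below 43%.** The study excludes men with known psychiatric disorders and uses a PHQ-9 cut-off of 10, whereas 43–58% comes from other studies. This stands and limits the claim that the full model is always feasible.

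**Conclusion.** The analysis as written does not test the three hypotheses as written. If any significant variable counts as support, false support arises in about 42%, 23% and 25% of null studies by domain and 67% overall with independent predictors; at correlation 0.3 the overall figure is 41–58% over 17 to 26 candidates. This is a multiplicity problem, and removing the screen alone would not cure it.

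The screen is a second, separate weakness. It makes the P values and intervals of retained variables too optimistic, and it can drop suppressed predictors, with a loss ranging from none to severe depending on a correlation the article does not give.

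The mismatch and the direction of both screening effects are firm. The sizes rest on assumptions: the candidate count, the 11/5/6 split (the conceptual framework figure is not available), the correlations and the masking scenario.

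**What to change.** - Drop the P < 0.25 step and fit one multiple logistic model with all listed variables, each assigned to a domain in writing.
- Test each hypothesis with a joint test of its domain block, Holm-adjusted over the three. Use a likelihood-ratio test, or a pooled Wald test if the data are multiply imputed, since the article names imputation as the likely handling of missing data.
- Report every adjusted odds ratio with its 95% confidence interval. Name predictors for the interviews, themes and joint display from the adjusted model at 0.05, and label them exploratory. The qualitative phase needs such a rule, so block tests alone are not enough.
- If prevalence turns out much lower than 43%, use a penalised fit rather than P-value screening.

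The cost is slightly wider intervals for correlated variables and a little more analysis work. No new data are needed. Whether the named SPSS version 25 covers pooled block tests or a penalised fit should be checked. The article puts the end of quantitative data collection at February 2023, so the change should be dated and recorded as made after data collection.
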